**Interventions**

CCBT: those randomized into this condition will complete 3 sessions a week, of 20 minutes each for a total of 16 weeks. CCBT will be conducted during normal work hours and delivered via the ‘*Spark*!’ online system directly to the subject’s normal work computer. This system is propriety software of The Brain Department.

The specific cognitive exercises in the CCBT program are equivalent to HappyNeuron Inc’s validated suite of 36 training options (under Australian and New Zealand exclusive license to The Brain Department). These exercises target the cognitive domains of memory, attention, language, executive functions and visuospatial abilities. A multi-domain approach is likely to be maximally effective as suggested by our recent systematic review 19. During each session, subjects will practice a number of exercises from across a range of cognitive domains, and gradually be challenged by exercises of greater complexity and cognitive demand during the course of the 4-month period in an individualized fashion prescribed by the system’s in-built algorithms.

Active Control: those randomized to this condition will view a series of educational National Geographic videos at their work station and answer related multiple choice questions delivered via an online survey. Frequency and duration of computer-based audiovisual stimulation matches the CCBT intervention and cognitive load has been minimised.

**Randomized**

**Volunteer**

**CCBT**

20 mins per session,

3 sessions a week, for 4 months

**Active Control**

20 mins per session,

3 sessions a week, for 4 months

**Proximal Follow-up**

Cognitive Tests

Mental Well being scales

Workplace Productivity review

**Longitudinal Follow-up**

Cognitive Tests

Mental Well being scales

Workplace Productivity review

**Baseline Assessment**

Cognitive Tests

Mental Well being scales

Workplace Productivity review

**Active Control**

Option to complete CCBT

**Figure 3.** *Trial Design*

**Outcome Measures**

As mentioned in Background, we will test CCBT rigorously against three ‘real-world’ sets of primary outcome variables. Background variables controlled for include age, gender and site. Outcome measures will be collected and supervised by a lead research organizational psychologist ([name]) who will remain blind to the training status of subjects.

1. Cognitive Capacities

Subjects will undergo a series of neuropsychological tests that will take no more than 1 hour, given the ATO’s preference to keep testing sessions brief. These will be administered in person by trained research psychologists and include:

1. Computer-based adaptation of WAIS-3 Matrix Reasoning 36: Form A and B will be counterbalanced at baseline and follow-up
2. A subset of tests taken from *Mindstreams*35*,* a validated computer-based neuropsychological assessment system: Verbal Memory, Non Verbal Memory, Staged Information Processing Speed, Visual-Spatial Orientation, Stroop Interference,
3. A subset of tests taken from *CogScreen*34,a validated computer-based neuropsychological assessment system: Visual Sequence Comparison, Divided Attention Parts I and II
4. Controlled Oral Word Association (COWAT): Form A (FAS) will be administered at baseline and Form B (CFL) at follow-up33

All tests each have alternate forms to minimize retest effects.

*Cognitive Primary Outcome Measures:* The following theory-based combinations of test outcomes will be calculated in the form of a sum of standardized z-scores to produce summary domain scores:

1. Memory: Verbal memory and Non-verbal memory
2. Attention: Divided attention Part I and Part II
3. Visual Spatial: Visual Spatial Orientation
4. Language: COWAT
5. Disinhibition: Stroop
6. Reasoning and problem solving: Matrix
7. Speed: Staged Information Processing Speed, Visual Sequence Comparison.

In addition, two *General Cognitive summary scores* will be calculated:

1. Average of domain scores
2. First principal component of baseline cognitive tests results

*Cognitive Secondary Outcome Measures:* Each individual cognitive test score.

2. Workplace Mental Wellbeing

We have operationalised workplace mental wellbeing to include 2 dimensions. Each is measured by a combination of internationally accepted and validated scale with known test-retest reliability and previous use in intervention trials.

1. Job Satisfaction:
   1. Overall job satisfaction scale 28 for positive appraisals
   2. Intention to quit scale 29 for negative appraisals
2. Psychological wellbeing:
   1. Relative absence of Psychological Distress: this will be measured by the Depression, Anxiety and Stress Scales (DASS27).
   2. Self-Esteem: Professional self esteem scale (as modified by Proudfoot et al 2009 30)
   3. Quality of Life: the Quality of Life Scale (QOLS 31) and Ryff’s Scales of Psychological Wellbeing (SPWB32)

These self report scales will be administered via email and online survey at baseline, proximal follow-up and longitudinal follow-up.

*Primary Outcome Measures:*  job satisfaction and psychological wellbeing will be calculated as the sum of standardized z-scores.

*Wellbeing Secondary Outcome Measures:* Each individual wellbeing score.

3. Workplace Productivity

In collaboration with the ATO we have identified the following productivity indicators:

1. average handling time
2. conversion rates
3. work quality ratings

These will be provided by the ATO for each individual at baseline (on the basis of the 6 months performance before starting the study), at proximal follow-up and at longitudinal follow-up (on the basis of approximately 12 months since commencement of the study).

*Productivity Primary Outcome Measure*: Overall productivity will be calculated as the sum of standardized z-scores across each productivity measure.

*Productivity Secondary Outcome Measures*: Each individual productivity measure.

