**Design**

A randomized, active controlled, single-blind, multi-centre intervention trial with longitudinal follow-up will be conducted. CONSORT criteria will be fully implemented in design and reporting. Subjects will be recruited, informed consent given, screened and then undergo a baseline set of assessments, followed by randomization (by computer generated sequence) to the CCBT arm or the active control arm on a 1:1 ratio. Subjectwise randomization will occur across all sites. Concealment of randomisation was achieved by central off-site administration and communicated via email. CCBT training will then commence for 16 weeks (4 months), followed by immediate proximal follow-up, and then longitudinal follow-up 6 months later (i.e., approximately one year since start of trial). The overall sequence of events is provided in **Figure 3**.

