**Statistical Analysis**

Analysis will be by intention-to-treat using a repeated measures mixed modeling approach. Primary outcomes will be considered separately within each set (i.e., cognitive, wellbeing and productivity). Both univariate and multivariate analyses accounting for multiple comparisons and background variables will be conducted. Absence of any differences on primary outcome measures between ATO work location would lead to collapsing data across sites, otherwise SITE will be entered in the model as a covariate. For each analysis, within-subject change will be tested (TIME), followed by between GROUP differences, and then the main analysis will test the interaction between TIME X GROUP. Statistical significance will be set at alpha = 0.05. Treatment of missing values will depend on the extent and randomness of incomplete data.

Planned Subgroup analysis

A planned subgroup analysis of individuals categorized as high versus low on baseline cognitive testing (by median split of cognitive performance) will be conducted to determine if outcomes interact with initial level of cognitive competency.

Exploratory analysis

Depending on the nature of the results, exploratory structural equations modeling analyses may be run to determine the nature of any positive effects with respect to interactions between cognitive, wellbeing and productivity outcomes.

Power & Sample Size

Based on pilot study findings, effect size estimates for the domains of Memory and Executive function are presented in the table below. Note that positive effects are the desired direction for accuracy outcomes, and negative effects for response time outcomes. *Relative Effect Siz*e refers the Cohen’s d effect size in CCBT group (Pre-Post mean difference divided by pooled variance) minus the effect size in the control group.

|  |  | **Memory** | Executive Function |
| --- | --- | --- | --- |
| **Cohen's Relative Effect Size *d*** | **Accuracy** | 0.65 | 0.39 |
| **Response Time** | -0.51 | -0.99 |
| **Required Sample Size (n per group)** | **Accuracy** | 36 | 102 |
| **Response Time** | 66 | 22 |

Given the range of effect sizes observed, the most conservative effect size of 0.39 (on Executive accuracy scores) has been chosen. Controlling power at 0.8, 102 subjects would therefore be required per arm (rounded down to 100). After inflation for an expected 10% attrition rate, this results in an initial sample of N=220, (each arm to comprise n= 110).

References

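### On its natural reading, the longitudinal productivity value includes the training weeks, so it cannot show cleanly whether an effect lasts after training

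*Protocol*

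**What the plan says.** The Workplace Productivity part of Outcome Measures has the employer supply three indicators per person (handling time, conversion, quality). One sentence sets the period for each time point:

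- Baseline: "at baseline (on the basis of the 6 months performance before starting the study").
- Proximal: named only as a time point, "at proximal follow-up and at longitudinal follow-up", with no period.
- Longitudinal: "at longitudinal follow-up (on the basis of approximately 12 months since commencement of the study").

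The primary productivity outcome combines the indicators: "Overall productivity will be calculated as the sum of standardized z-scores across each productivity measure".

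The Design section gives the calendar. On the training course and the first visit after it, the text reads: "CCBT training will then commence for 16 weeks (4 months), followed by immediate proximal follow-up". The later visit is placed by its distance from the first and by a label: "longitudinal follow-up 6 months later (i.e., approximately one year since start of trial").

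Under Statistical Analysis, "the main analysis will test the interaction between TIME X GROUP".

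**The concern.** Productivity comes from accumulated employer records, so each value needs a defined stretch of time behind it. At baseline the protocol introduces that stretch with a phrase that plainly means a look-back period. The same phrase then introduces the longitudinal value, so the natural reading is again a period, this time running forward from study start.

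Such a period takes in the whole training course. The longitudinal value would then mix performance during training with performance after it, and would share data with the proximal value. It would not be a separate third time point for the test of time by group. It would also cover up to twice the baseline length (12 months against 6), so its precision would differ.

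At stake is the question that a later follow-up exists to answer: whether any productivity gain outlasts the training. Productivity is one of the three primary outcome sets.

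**Working it through.** **Inputs.** Training 16 weeks, which the protocol rounds to 4 months; proximal follow-up immediately afterwards; longitudinal follow-up 6 months later (all from Design). Baseline period 6 months, longitudinal basis about 12 months, proximal period not stated (all from Outcome Measures). One month is taken as 4.348 weeks.

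**1. The protocol's own timing.** 16 / 4.348 = 3.68 months of training. 3.68 + 6 = 9.68 months, or 4 + 6 = 10 with the protocol's rounding. The stated figure is about one year. Counted from the start of training it is not reproduced: the gap is 12 − 9.68 = 2.3 months, or 12 − 10 = 2.0 months.

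**2. Share of the longitudinal window that is training time.** w = training length / window length.

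- 12-month window: 3.68 / 12 = 0.31.
- Records stop at the implied visit: 3.68 / 9.68 = 0.38.
- Window limited to the 6 months after proximal follow-up: 0 / 6 = 0.

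**3. Effect on the estimate.** Assume that every month counts equally. Let E_T be the mean group difference during training and E_P the mean difference afterwards, both on the indicator's own scale. The window average is w × E_T + (1 − w) × E_P.

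| Pattern of effect | 12-month window | 9.68-month window | 6 months after proximal |
|---|---|---|---|
| Only after training (E_T = 0), as share of E_P | 0.69 | 0.62 | 1.00 |
| Linear build-up in training (E_T = 0.5 × E_P), as share of E_P | 0.69 + 0.5 × 0.31 = 0.85 | 0.62 + 0.5 × 0.38 = 0.81 | 1.00 |
| Only during training (E_P = 0), as share of E_T | 0.31 | 0.38 | 0 |

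The distortion runs in both directions: dilution in the first two rows, apparent persistence in the third.

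**4. Overlap with the proximal value.** No proximal window is given, so its overlap cannot be computed. Two illustrations, taking commencement as the start of training:

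- If the window is the 16 training weeks, all 3.68 months are counted again at longitudinal follow-up.
- If it is a 6-month look-back like baseline, 6 − 3.68 = 2.32 months fall before training and inside the baseline period, and the other 3.68 months are counted again.

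**The case against.** **The wording may name a date and not a period.** Design labels the longitudinal visit in almost the same terms, so the productivity text could simply mean the value at about 12 months. This stands as a caution: the cumulative reading is an inference. It remains the more natural one, because the same phrase in the same sentence introduces a period at baseline. On the other reading the longitudinal value has no stated window at all, and the same fix is needed.

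**Extraction windows are usually left to an SAP.** That holds for detail the protocol leaves open. Here the protocol itself fixes the longitudinal basis, and following it as written gives a poor answer on persistence.

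**Aim 3 can still be tested.** True. The comparison of baseline with proximal follow-up does not use the longitudinal window.

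**Stronger readings that a reader might infer, and that the documents do not support:**

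- *That the longitudinal window contains the whole proximal period.* No proximal period is stated, and a 6-month look-back would begin before training.
- *That Design and Outcome Measures contradict each other on timing.* Both say about 12 months or one year. The looseness lies inside Design, between its intervals and its label. Screening and baseline testing, of unstated length, could close part of the gap if they count as trial time.
- *That power falls by a known amount.* The effect size of 0.39 under Power & Sample Size is a pilot estimate for executive accuracy. The protocol makes no power claim for productivity, so there is no figure to correct.

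**Conclusion.** The point holds on the natural reading of the text. As written, the longitudinal value of a primary outcome is 31% to 38% training time and counts again any post-start data behind the proximal value. It therefore cannot separate an effect that lasts from one that ends with training. This rests on reading the longitudinal basis as a period from study start, on taking commencement as the start of training, and on equal weight for each month. The percentages in the table describe the raw group difference; standardising the indicators could change the scale but not the mixing.

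The change should be made, but the fault is limited to the question of persistence. The 10-versus-12-month looseness in Design is a minor matter of wording.

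**What to change.** State start and end dates for all three productivity windows, and do so before any unblinded data are seen, because a later choice would allow selection on a primary outcome:

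- **Baseline:** the 6 months before the study, as now.
- **Proximal:** a fixed window ending at proximal follow-up and not reaching back before the start of training.
- **Longitudinal:** only the 6 months between proximal and longitudinal follow-up. This holds no training time and matches baseline in length.

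In Design, give the longitudinal follow-up date from one defined start point, so that 16 weeks plus 6 months and the one-year label agree, and use the same start point in Outcome Measures.

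The cost is a revised data request to the employer, which already supplies these indicators, and a few sentences of protocol text. The downside is that a 6-month mean is somewhat noisier than a 12-month mean.

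### The job satisfaction and productivity primary outcomes are sums of z-scores of components that run in opposite directions, and no sign reversal is stated

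*Protocol*

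**What the plan says.** All of this stands in the Protocol under Outcome Measures.

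- **Productivity (item 3).** The indicators agreed with the employer are "average handling time", "conversion rates" and "work quality ratings". The single primary outcome is built from them: "Overall productivity will be calculated as the sum of standardized z-scores across each productivity measure".
- **Wellbeing (item 2).** There are two primary outcomes: "job satisfaction and psychological wellbeing will be calculated as the sum of standardized z-scores". Job satisfaction has two scales. The overall satisfaction scale is said to capture positive appraisals. The other is listed as "Intention to quit scale 29 for negative appraisals". Psychological wellbeing combines the DASS, a professional self-esteem scale, the QOLS and the Ryff scales. The DASS is entered under a label that names the absence of distress.
- **Secondary outcomes.** Each wellbeing score and each productivity measure is also a secondary outcome in its own right.

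Direction is addressed explicitly in one place only, Power & Sample Size, where the pilot effect sizes are introduced: "Note that positive effects are the desired direction for accuracy outcomes, and negative effects for response time outcomes". No sentence carries such a convention into the composite scores.

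**The concern.** A sum of z-scores measures benefit only if a higher value is better on every component. Here the written rule adds components of opposite polarity. A worker who becomes more satisfied and less inclined to quit moves up on one job satisfaction component and down on the other. A worker who handles cases faster, converts more and is rated higher gains on two productivity components and loses on the third.

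Overall productivity is the only productivity primary outcome, and job satisfaction is one of only two wellbeing primaries. A scoring rule that shrinks, removes or reverses a real effect therefore bears directly on how the trial's second and third aims would be reported. If the signs were chosen only after the group results had been seen, that choice could decide whether these outcomes succeed.

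**Working it through.** **The plan's own figure.** The Protocol gives no power figure for the composites. Its sample size rests on d = 0.39 for executive accuracy at power 0.8. With two-sided alpha 0.05 (sidedness is not stated), n = 2 × (1.960 + 0.842)² / 0.39² = 103.2, so 104 per arm. The Protocol states 102, rounded down to 100. This is close enough to count as reproduced. It does not depend on the composites, so the point leaves it unchanged.

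**Assumptions for the check (not in the Protocol).** Each component has SD 1. Training gives the same benefit d on each component, in that component's better direction. The components have a common correlation r, measured after all are turned to the better direction, with r = 0 to 0.5.

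**Formula.** Let s = +1 for a component added in the better direction and -1 for one left unreversed. The composite effect in SD units is

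d × Σs_i / √(Σ_i Σ_j s_i s_j r_ij).

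**Job satisfaction (two components, one opposed).**
- Aligned: 2d/√(2 + 2r).
- As written: (1 − 1)d/√(2 − 2r) = 0 at every r below 1.

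**Productivity (three components, one opposed).**
- Aligned: 3d/√(3 + 6r).
- As written: d/√(3 − 2r).

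| r | Aligned | As written | Share kept |
|---|---|---|---|
| 0 | 1.732d | 0.577d | 33% |
| 0.3 | 1.369d | 0.645d | 47% |
| 0.5 | 1.225d | 0.707d | 58% |

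**Illustration.** Take d = 0.39 on every component, 100 per arm and a simple two-group comparison.
- Productivity: the aligned effect is 0.68, 0.53 and 0.48 at r = 0, 0.3 and 0.5, with power 99.8%, 96.5% and 92.2%. As written it is 0.23, 0.25 and 0.28, with power 36%, 43% and 50%.
- Job satisfaction: the aligned effect is 0.55 to 0.45, with power 97% to 89%. As written it is 0, so the test rejects only at its 5% error rate.

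**Benefit on handling time alone.** If handling time falls by d and the other two measures do not move, the composite as written changes by −d/√(3 − 2r). For d = 0.39 that is −0.23 (r = 0) to −0.28 (r = 0.5). Aligned, it is +d/√(3 + 6r), or +0.23 to +0.16. The sign is reversed.

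**Psychological wellbeing, if the DASS total were left unreversed (one of four).**
- Aligned: 4d/√(4 + 12r).
- As written: 2d/√4 = d.
- Share kept: 50%, 69% and 79% at r = 0, 0.3 and 0.5. With d = 0.39, power as written is still 79%.

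The planned analysis is a repeated-measures mixed model testing TIME X GROUP. The power figures are therefore illustrative. The cancellation in the numerator is not specific to a two-group test: a difference in mean change on a sum is the sum of the differences on its components.

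**The case against.** The strongest reply is that silence is not error. The Protocol does not say that raw, unreversed scores are summed. Reverse-scoring is often left to a statistical analysis plan, which is not at hand. An analyst building a score called job satisfaction would probably reverse intention to quit without being told. The authors were plainly aware of polarity: they label the two job satisfaction scales as positive and negative, and they note opposite desired directions for the pilot data.

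Much of this stands. Cancellation is conditional on literal application. The direction of handling time is inferred, since no sentence states it. For the DASS, the label points to an intended reversal, so that component needs the reversal spelled out more than corrected. What does not stand is that scoring was left open. The Protocol gives the formula for each of these primary outcomes, and a later plan that followed it exactly would reproduce the problem.

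Two stronger readings are tempting, and the documents do not support them.

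- A reader might infer that the cognitive domain scores cancel too, for example "Speed: Staged Information Processing Speed, Visual Sequence Comparison". The Protocol does not say whether a time or an accuracy score is taken from each test, so opposed directions within a domain are not shown. Four of the seven domains list a single test. The general score based on a first principal component takes its loadings from the data and is not a plain sum.
- A reader might infer that the wellbeing and productivity aims could not be answered at all. Each component is analysed separately as a secondary outcome, and multivariate analyses are planned, so component effects would remain visible.

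**Conclusion.** The point holds for job satisfaction and productivity: the scoring rule is fixed without a sign convention, although the components run in opposite directions. Job satisfaction is the clearest case, because the Protocol itself labels the polarity of its two scales. If the rule is followed as written, and benefit is equal on all components, the job satisfaction effect vanishes and productivity loses roughly two fifths to two thirds of its effect. Unequal benefits would change these figures, and with benefit on handling time alone the sign reverses. Psychological wellbeing is a lesser instance that calls for clarification. The documents do not show that the scores will in fact be computed without reversal. The point concerns what the text prescribes, and neither the design nor the sample size is affected.

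**What to change.** Add one sentence to the wellbeing and productivity primary outcome definitions under Outcome Measures: before summing, every component is signed so that a higher value means a better outcome, with the z-scores of average handling time, intention to quit and the DASS multiplied by -1. The sponsor should confirm with the employer that shorter handling time is the better direction, and record this in the same place. The sentence should be in force before any unblinded analysis, so that the signs cannot depend on the results. It costs one sentence in the Protocol, repeated in the analysis plan if there is one, and needs no new data.
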